#### Reasons for early study termination

Continued analysis for safety will be performed regarding the presence of major adverse events, and an interim analysis will be formed after every five patients are included. Major adverse events are defined as postoperative complications requiring active treatment (the Clavien-Dindo classification grade III and above). In case of exclusion, patients are offered standard treatment according to hospital standards. The study will be terminated early if this analysis reveals the presence of major adverse events in 50% or more in one arm of the study. The Danish Patient Compensation covers patients enrolled in this study.

Only the project assistant who developed the study database and monitors the data will have access to the interim analysis. This assistant will extract a predefined report containing only reported adverse events, ensuring that all other data remains confidential. If adverse events are identified, they will be presented to the study group, including the principal investigator, and an audit will be performed before deciding whether to terminate the trial. There will not be a possibility of modifying the intervention, but patients will receive standard treatment.

## Ethics and dissemination

### Research ethics approval

The study protocol, version 8, was approved by the Regional Committees on Health Research Ethics for Southern Denmark on June 27, 2024 (S-20230073), registered by the Danish Data Protection Agency (Journal nr.: 24/26916) and by the ClinicalTrials.gov (NCT06505135).

The study will be conducted according to the study protocol, which conforms to the current health legislations and good clinical practice (ICH-GCP), and written informed consent will be obtained from the participants before participation in the study (Additional file 3). Participation is voluntary, and patients may withdraw their consent at any time without consequences for further treatment. The data collected from discontinued patients will be deleted and will not be part of the analysis.

To protect patient confidentiality, the personal data collection will be registered in the REDCap electronic database [27], data extraction for data analysis will be pseudonymized, and the results data will be presented anonymously. The patient will be informed both verbally and in writing that the tissue sample will be stored in a research biobank at the Department of Pathology in Odense, along with details about any future analyses. Participants will have no financial gain by participating in the study. The advantage for the patients may be improved rehabilitation and reduced risk of fibrosis. Stem cell therapy has, however, been shown to be safe. Intra-articular injection of the lipoaspirate is formerly approved to be used at Hvidovre Hospital (Danish National Committee on Health Research Ethics (H-18013145) and the Danish Data Protection Agency (VD-2018–141)). This study can potentially establish the fundaments of a safe treatment for an otherwise difficult surgical condition.

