##### Primary analysis

The primary analysis will be a beta-binomial mixed effect model, thus adopting a subject-specific approach. We will incorporate an interaction between group and time if necessary, to accommodate varying treatment effects over the time period. Therefore, we will present the estimates for each time point (baseline, at 3, 6, and 12 months) and construct a margin plot based on the model. We will conduct a likelihood ratio test to test whether our intervention affects the primary outcome across all time points. If the test is statistically significant, we will conduct a *z*-test at each time point to assess when there is a statistically significant treatment effect. Here, we will utilize G-computation to acquire interpretable effect sizes on both the mean ratio and mean difference scales for sensitivity purposes. In the G-computation, the Q-model will be a mixed-effect model, and the prediction will be based solely on the fixed effect. To avoid inflating the type I error rate in the bootstrapped *z*-test, we will adjust the *z*-test for multiple tests.

If the beta-binomial regression has difficulties converging, we will adopt a mixed-effect model with bootstrapped confidence intervals. Here, we will choose restricted maximum likelihood and the Kenward method for calculating the degrees of freedom and test whether a random slope shall be incorporated by way of an *F*-test.

The primary analysis will follow the intention-to-treat principle; hence, missing data will be managed. As the beta-binomial mixed effect model regression uses maximum likelihood estimation, we can assume that the beta regression will yield unbiased results if the data is missing at random or completely at random. However, under the assumption of missing not at random, the estimates from the beta regression will be biased; therefore, we will conduct joined modeling to assess the influence of missing data if the data was missing not at random. In the joint model, we will use Cox regression to estimate the censoring weights.

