### Adverse events, complications, and risks

The liposuction procedure is safe with a very low risk of complications (less than 1%), such as bleeding, infections, and scarring [40]. In rare cases, there may be bleeding, and a reoperation or puncture of the skin may be necessary. An infection is rarely seen and can be treated with antibiotics, and in exceptional cases, additional surgery may be required. Sensory disturbances might be seen at the donor site. These fade away generally within 3–6 months, but in some individuals, it may be permanent (less than 1%).

Harvest of 0.1–0.2 g muscle biopsies from the supraspinatus muscle is performed under direct vision from the arthroscope and has been performed without complications in 42 patients in a former protocol (Projekt-ID: S-20160037).

MRI and ultrasonography have no reported risks or adverse effects.

The responsible surgeon or physician will report adverse events in the study database at the time they occur. All adverse events occurring during surgery, post-surgery, and up to the final follow-up at 1 year will be documented. Adverse events that occur after a subject has been discontinued from the study will not be reported unless the investigators suspect they are related to the stem cell treatment procedures. We will record adverse events and any negative effects of the intervention using a structured template that allows for additional comments in free text within the electronic database (REDCap). For each event, we will document the date, type of adverse event, or negative effect (e.g., infection, skin and subcutaneous tissue disorders, increased pain, reduced strength, reduced mobility, reduced sensitivity, or other issues). Any identified harms will be detailed in future publications.

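### Deleting the data of discontinued patients conflicts with the planned intention-to-treat analysis and, read literally, with the adverse event plan; it may bias the 12-month comparison

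*Protocol article*

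**What the plan says.** Research ethics approval states that "patients may withdraw their consent at any time without consequences for further treatment", and continues: "The data collected from discontinued patients will be deleted and will not be part of the analysis". The term used is discontinued patients, which the article does not define. Nothing is said about scores or adverse events already recorded.

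Primary analysis states: "The primary analysis will follow the intention-to-treat principle; hence, missing data will be managed". It justifies the beta-binomial mixed model by maximum likelihood, so that "we can assume that the beta regression will yield unbiased results if the data is missing at random or completely at random", and adds joint modelling in case data are missing not at random.

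Adverse events, complications, and risks states: "All adverse events occurring during surgery, post-surgery, and up to the final follow-up at 1 year will be documented". It also states: "Adverse events that occur after a subject has been discontinued from the study will not be reported unless the investigators suspect they are related", the relation in question being to the stem cell procedures. Identified harms are to be published.

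Reasons for early study termination bases a safety rule on the share of an arm: "The study will be terminated early if this analysis reveals the presence of major adverse events in 50% or more in one arm".

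**The concern.** The article gives two incompatible rules for the same patients. A likelihood model is protected under missing at random because it uses the baseline, 3-month and 6-month scores of patients who lack a 12-month score. A joint model needs the histories of those who left. Erasing a patient removes both. Deletion also cannot be undone, so the conflict cannot be settled at the analysis stage.

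The design makes informative leaving plausible. Allocation is revealed before surgery; patients, physicians and outcome adjudicators are unblinded; the primary outcome is self-reported. Each patient is 1/15 = 6.7% of an arm, and the sample size section states no allowance for dropout.

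On safety, literal deletion would remove recorded events from the final harms report and could change the share on which the 50% rule depends. Separately, the rule for events after discontinuation treats the arms differently: control patients have no stem cell procedure to which an event could be related.

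**Working it through.** **1. The plan's own figure.** Inputs from Table 1 of the protocol article: 12-month means 33 and 41, SDs 4.12 (control) and 3.6 (intervention), 15 per arm, stated power 94%. The Stata file is not shown, so the model form is an assumption: linear regression with group-by-time terms, independent observations, pooled residual variance, two-sided test of the 12-month interaction against baseline at 0.05/3. Simulation with 100,000 runs gives 93.6%, which reproduces the stated 94%. (A plain two-sample t-test at 12 months at 0.05/3 gives about 99.8%, so the figure depends on the model form.)

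**2. Power after deletion (assumed losses, same test).**

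| Patients deleted | One arm only | Each arm |
|---|---|---|
| 1 | 92.6% | 91.5% |
| 2 | 91.3% | 89.2% |
| 3 | 89.7% | 86.1% |

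Part of this loss would occur anyway if the 12-month values were missing. Power is not the main issue.

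**3. Bias with no true effect.** Assume that the m lowest scorers of 15 intervention patients are deleted and no controls, with SD 4.12 in both arms.

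Bias = SD × (sum of the m largest expected normal order statistics for n = 15) / (15 − m). The order statistics are 1.736, 1.248 and 0.948.

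- m = 1: 4.12 × 1.736/14 = 0.51
- m = 2: 4.12 × 2.984/13 = 0.95
- m = 3: 4.12 × 3.932/12 = 1.35

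This is the extreme case, where deletion follows the 12-month score itself. Simulation agrees (0.51, 0.95, 1.35). The type I error of an unadjusted two-sided 5% t-test rises to 7.0%, 10.6% and 15.9%.

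If deletion instead follows the 3-month score, multiply by the 3-to-12-month correlation (0.3 to 0.7 assumed). The smallest case is 0.3 × 0.51 = 0.15 (simulated 0.16 to 0.17). The largest is 0.7 × 1.35 = 0.95 (simulated 0.94 to 0.95). Type I error runs from 5.1% to 9.8%.

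**4. Same setting, partial data kept.** With the 3-month scores retained and maximum likelihood used, the simulated bias is −0.01 to +0.02 points, that is, about 0. This is the protection that the plan claims and that deletion removes.

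**5. Safety share.** These counts are illustrations, not forecasts.

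- 8/15 = 53% meets the 50% rule. Deleting two patients who had events gives 6/13 = 46%, which does not.
- In an arm of 8, 4/8 = 50% becomes 3/7 = 43% after one such deletion.
- The opposite can also happen: 7/15 = 47% becomes 7/14 = 50% if one event-free patient is deleted.

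**The case against.** The deletion sentence directly follows the one on withdrawing consent, so it may have been meant for withdrawn consent only. Patients who miss visits are handled separately, with reminders and active contact, and need not count as discontinued. This part of the objection stands. A reader might infer that the analysis becomes a completers-only comparison, with no partial records for the mixed model and no dropouts for the joint model. That follows only if every patient who leaves follow-up counts as discontinued, and the article does not say so. The conflict survives the narrow reading, because a patient who withdraws consent was still randomised, and the wording used is broader than withdrawal. The adverse event section also speaks of subjects discontinued from the study.

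A reader might also infer that adverse events will certainly be lost. The deletion sentence does not name them; the adverse event section says they are entered when they occur and that harms will be published; and the review after every five inclusions could show events before any deletion. What stands is a contradiction on literal reading, to be reconciled. The safety illustrations also need an arm already near the threshold.

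Finally, a reader might object to the sentence "In the joint model, we will use Cox regression to estimate the censoring weights" on the ground that weights built from observed data do not address data missing not at random. The wording is unclear, but the plan names joint modelling, a recognised approach to that problem, with a Cox model as a usual dropout component. The documents do not show that only weighting is intended, so this is not part of the point.

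**Conclusion.** The textual conflict is firm: as written, randomised patients and their earlier data are removed from an analysis described as intention-to-treat, on either reading of discontinued. The different treatment of the arms for adverse events after discontinuation is also firm.

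The bias is conditional. It is zero in expectation if leaving is unrelated to arm and outcome. With 1 to 3 intervention patients deleted for poor scores it is about 0.2 to 1.3 OSS points, at most about a sixth of the 8-point target (1.35/8 = 17%). These counts and the correlations are assumptions, since the article gives no dropout rate. Larger figures need a score gap that the documents do not supply: a 2-point bias from 3 of 15 patients requires a 10-point gap (3/15 × 10), which exceeds the target difference and is 2.4 to 2.8 of the Table 1 SDs (10/4.12; 10/3.6).

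The matter should be settled before any record is deleted, because the loss cannot be reversed.

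**What to change.** Replace the deletion sentence and reconcile it with the analysis and adverse event sections:

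- Define discontinuation, and separate stopping treatment or visits from withdrawing consent to the use of data.
- Keep scores and adverse events collected up to discontinuation, as far as consent and law allow, and analyse them in the randomised arm.
- Delete records only on an explicit erasure request, and report the number of such deletions by arm.
- Apply the same adverse event reporting rule after discontinuation to both arms.
- State whether patients whose records are erased stay in the numerator and denominator of the safety share.

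The cost is a wording change in the protocol and possibly in the patient information, with ethics committee notification or approval. The consent form is not shown. If it promises deletion, the committee would have to say how patients already enrolled are handled. No additional patients or visits are needed.

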### Protocol amendments

Any important protocol modifications will be directly communicated to cooperators, registered in the national clinical trials register and ethical committee, and be clearly stated in future publications.

### Ancillary and post-trial care

The procedures are known to have minimal risks and the hospital will provide post-trial care as routinely.

### Dissemination policy

The results whether negative or positive will be presented to all stakeholders and will be published in an open reviewed journal. Substantive contributions to the design, execution, interpretation, and reporting of the clinical trial will be acknowledged with authorship on the final trial report, in accordance with the guidelines of the International Committee of Medical Journal Editors (ICMJE).

### Biological material storage biobank

During the study period, acquired biological materials from participating patients will be registered and stored in the research biobank at the Department of Clinical Pathology, OUH, according to current legislations and requirements. The materials include aliquots of freshly isolated micro-fragmented adipose tissue products and processed products hereof to enable analyses and comparisons with clinical efficacy. After the study is completed, stored materials are transferred to a biobank for future research. Future research will involve analyses of the cellular content, with the aim of comparing the cell composition to the treatment outcomes and to investigate how freezing affects fat-derived stem cells, with a focus on potential phenotypic changes in their differentiation capacity.

## Discussion

Treatment of rotator cuff tears with micro-fragmented adipose tissue is a minimal-invasive procedure with the potential to shorten and ease recovery, accelerate return to daily activity and work of thus with a potential capacity to improve the functional result compared to conventional surgery alone.

The study will provide evidence whether addition of micro-fragmented adipose tissue therapy can augment conventional rotator cuff tear treatment. The study will also reveal whether this treatment can be feasible for standard care of patients with rotator cuff tear as it will be simple to standardize. Moreover, besides providing a novel treatment for patients with rotator cuff tears, the project will based on data from muscle biopsies and scanning modalities generate new knowledge, preparing for precision regenerative medicine in shoulder disease. We expect that we after the project period will be able to initiate a phase 2 clinical trial to further implement precision medicine as a standard treatment for patients suffering rotator cuff tear. The results of the study will have both national and international interest, as this stem cell treatment can easily be applied in hospitals with a similar context and resources.

## Trial status

ClinicalTrials.gov: NCT06505135.

Protocol version number 8. Date: 22.06.2024.

Date start of recruitment: September 1, 2024.

Approximate date recruitment to be completed: approx. December 2025.

## Data Availability

Due to Danish laws on personal data, data cannot be shared publicly. To request these data, the corresponding author must be contacted for more information. The person responsible for the research was the principal investigator and corresponding author ([name]) who together with the Department of Health Research and the University Hospital of Southern Denmark, owns the data and has access to the final data set.

## Abbreviations

PROM: Patient-reported outcome measure
RCT: Rotator cuff tear
